### Objectives {7}

#### Primary objectives

To evaluate if withholding treatment with metformin in women, with type 2 diabetes or gestational diabetes (GDM) pregnancy AND risk factors for placental disease, affects foetal growthTo determine what impact metformin has on early postnatal growth and metabolic function, in infants born to women with poor cardiometabolic health

#### Secondary objectives

To investigate the effect of metformin treatment on placental function and measures of maternal cardiometabolic healthTo determine the impact of metformin on early postnatal growth and metabolic function, in infants born to women with poor cardiometabolic healthTo determine if maternal exposure to metformin during pregnancy improves maternal cardiometabolic health status 1 year after pregnancy

### Trial design {8}

MIMICH is a phase III, two-arm, single-centre, open-label pragmatic randomised controlled trial (RCT). The study framework aims to assess the superiority of withholding metformin in otherwise standard pregnancy diabetes care, determined by foetal growth trajectory and placental function. Randomisation will take place in a 1:1 ratio. Following the RCT, participants who provide consent will be enrolled in an observational cohort study assessing postnatal maternal and infant cardiometabolic health, with follow-up visits at 3–6 months and again at 12–48 months postpartum.

## Methods: participants, interventions and outcomes

### Trial setting {9}

The study is conducted within Manchester University NHS Foundation Trust (MFT) (single Hospital Trust). Women will initially be identified in antenatal clinics at three hospital sites within MFT (St Mary’s Oxford Rd, St Mary’s Wythenshawe, North Manchester General Hospital) and provided with information regarding the study. Confirmation of eligibility, consent and all study visits will take place within the Maternal & Fetal Health Research Centre, St Mary’s Oxford Rd. Pregnancy outcome data will be collected following review of clinical records by study midwives within MFHRC with assistance from CRN research staff at each of the identification hospital sites. Participation in the postnatal follow-up study will be offered to participants who consent to be contacted about future research. All procedures including screening, consent and study visits will take place at St Mary’s Hospital MFT by a delegated member of the research team.

Participants will continue to receive the standard pathway of care throughout the course of the trial, with the exception of the omission of metformin therapy for those participants randomised to the intervention arm.

### Eligibility criteria {10}

#### Inclusion criteria

Singleton pregnancy between 6^+0^ and 30^+0^ weeks’ gestation inclusiveAged 18 years or over and willing and able to give informed consentDiagnosis of diabetes in pregnancyType 2 diabetes diagnosed before pregnancy ORType 2/GDM diagnosed < 24 weeks’ gestation: abnormal glucose tolerance test^a^, abnormal HBGM^b^ and/or HbA1C ≥ 41 mmol/L ORGDM (diagnosed 24–30 weeks): HbA1C ≥ 41 mmol/L and/or abnormal glucose tolerance test^a^Abnormal HBGM.^b^ (≤ 30 weeks)Presence of at least one risk factor for placental diseaseBP ≥ 130 and/or ≥ 80 mmHg (clinic blood pressure)Pulse wave velocity ≥ 9 m/sAge ≥ 35 yearsNulliparousPre-eclampsia and/or small for gestational age (< 10th centile) in a prior pregnancyCurrent SGA (EFW < 10.th centile)Mean uterine artery PI ≥ 95th centile^c^Placental growth factor < 10th centile^c^EFW ≤ 50th centile (if ≥ 22 weeks)^c,d^

^a^Abnormal glucose tolerance test: fasting glucose ≥ 5.3 mmol/L and/or 2 h ≥ 8.5 mmol/L.

^b^Abnormal home blood glucose monitoring (HBGM): 3 abnormal readings (fasting blood glucose ≥ 5.3 mmol/L, 1 h post meal ≥ 7.8 mmol) in 1 week.

^c^To be confirmed/measured at the baseline visit.

^d^WHO population centiles [43].

#### Exclusion criteria

Medical contraindication to metforminKnown diagnosis of type 1 diabetesMultifoetal pregnancyPrior pregnancy complicated by shoulder dystociaKnown foetal abnormality identified prior to consentAny neonate confirmed to have a serious congenital or chromosomal abnormality or any congenital abnormality which may impact postnatal growth will be excluded from MIMICH II

### Eligibility of those performing interventions {10}

Study instruments and procedures are implemented by the team providing clinical care to the participants in the consultant-led clinic. This comprises of research midwives, dietitians, diabetic and specialist nurses/midwives with the relevant professional degrees and advanced training to fulfil their clinical role, locally trained research practitioners, and obstetricians/endocrinologists medically qualified with higher speciality postgraduate training.

### Who will take informed consent? {26a}

Women who meet the inclusion criteria are identified and approached by members of the direct clinical care team or the antenatal diabetes team (who are integrated within the direct clinical care team) at antenatal clinics. Potential participants are provided with information on the study, both verbally from a member of the research team and written via the participant information leaflet. Participants are given the opportunity to ask any questions they may have and then provided with appropriate time to decide whether they wish to participate. Eligibility is confirmed by a medically qualified individual. Consent is obtained by an appropriately trained healthcare professional (who is Good Clinical Practice (GCP) trained and designated to take consent by the site principal investigator). Study participation and prescription information is documented and communicated as per usual care.

### Additional consent provisions for collection and use of participant data and biological specimens {26b}

The consent forms include statements confirming permission for data collected during the study to be accessed by members of the maternal and foetal health centre, who may not be directly involved in care and/or members of the university or regulatory bodies where relevant to the research, and that collected data will be anonymised and included in publications related to the trial.

Additionally, the MIMICH consent form also includes statements confirming the collection of blood and placenta samples and their storage and distribution within the maternal and foetal health research centre.

Additional consent is obtained for participation in the follow-up postnatal study (MIMICH II).

The MIMICH II consent forms contain statements relating to the collection and storage of infant blood samples and to the collection and storage of maternal blood samples.

## Interventions

### Explanation for the choice of comparators {6b}

The comparators are diabetes treatment with or without metformin. Dietary and lifestyle modification with insulin treatment where required are standard components of treatment that will be provided to all participants in both arms, with the only difference being the use of metformin. Withholding metformin and normalising blood glucose levels with insulin alone will enable the impact of metformin on foetal growth and maternal and infant cardiometabolic health to be investigated.

### Intervention description {11a}

Standard diabetes care follows the recommendations in NICE guidance NG3: ‘Diabetes in pregnancy: management from preconception to the postnatal period’. Home blood glucose monitoring (HBGM) may be either intermittent capillary glucose measurement or continuous glucose monitoring (CGM). Glucose targets, as per NICE, are fasting, 5.3 mmol/L and 1 h post-prandial, 7.8 mmol/L. Metformin is commenced where these targets are not met with diet and lifestyle advice/modification (in line with NICE guidance and guided by dietitian referral). Metformin dose is titrated to maternal tolerance as well as glycaemic control, starting at 500 mg twice daily with meals, increased every 3–5 days up to a maximum of 2500 mg daily in divided doses. Insulin is introduced where glucose targets are not met having reached the maximum tolerated dose of metformin. Insulin prescription is tailored to individual glycaemic profile using a long-acting (detemir or isophane) or rapid-acting (aspart) insulin, in isolation or combination. Insulin dose changes will be recommended to participants at a minimum of 3-day intervals according to HBGM as per standard clinical care. Diabetes treatment is supervised by a team of specialist midwives, obstetricians and diabetologists.

### Criteria for discontinuing or modifying allocated interventions {11b}

Usual clinical care will be provided (following local and NICE guidelines), and medication will be titrated to glucose levels; no trial-specific treatment modifications are planned. Stopping or switching diabetes treatments is a common part of usual clinical care in pregnancy, and in order to maintain safety, it is anticipated that some participants will need to take metformin in the intervention arm. In addition, some participants allocated to usual care will not be able to tolerate metformin. Failure to tolerate metformin (usual care arm) will not be reported as an adverse event unless related to a reportable serious adverse event. All modifications to treatment allocation will be documented and included as secondary outcomes. A participant can continue in the study after discontinuation of treatment.

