### Outcomes {12}

#### MIMICH

Outcomes will be recorded in the electronic case report form, hosted on REDCap. Outcomes will be collected from baseline to maternal discharge post-birth. Neonatal outcomes will be recorded up to 28 days after birth.

Primary outcome:

Third trimester foetal growth velocity, assessed by change in foetal growth z-score between 20 and 29 weeks’ gestation (average) and birth.

At each scan, the estimated foetal weight (EFW) in grams will be calculated using 2D biometry and fractional thigh volume (TVol) measurements using a standard formula [44] and converted to a z-score [43]. The delta change in z-score between the average z-score of scans performed between 20 and 29 weeks and the birthweight z-score will be calculated.

Secondary outcomes:

During pregnancy, secondary outcomes will be reported as per standard for pregnancy intervention trials. Secondary foetal growth and birthweight analyses will be assessed according to treatment group in line with the primary outcome analysis. Outcomes relating to blood glucose control (as an indicator of treatment effect) will similarly be compared between groups, as will blood pressure and hypertensive complications. Reporting and analysis of secondary outcomes will be described in full in the statistical analysis plan; to avoid issues of multiple testing, not all secondary outcomes will be compared between treatment groups. Secondary outcomes will be assessed using adjusted linear regression for continuous outcomes and chi-squared for categorical outcomes; *p* values > 0.01 and < 0.05 will be interpreted with caution. Where appropriate, outcomes will be presented with a treatment effect and confidence intervals; other outcomes will be presented with summary statistics only.

Prespecified secondary outcomes:

Adherence/acceptability:Number of missed doses—calculated as an average over pregnancy from the number of missed doses reported in the 7 days prior to each study visit (adjusted for number of study visits)Number of women unable to comply with allocated treatment (cross over)Undesirable effects of allocated treatment (number of women reporting undesirable effects associated with metformin and/or insulin/number of women receiving metformin or insulin treatment)Treatment satisfaction with allocated medication regime (questionnaire)Acceptability of allocated medication regime (questionnaire)

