#### Adverse events

Adverse event recorded (number of women and number of adverse events) during treatment only. All AEs and SAEs identified will be recorded in the trial database and will be reviewed and signed by the PI. The trial sponsor will also be made aware of any SAEs that occur on trial and will be sent copies of the completed SAE forms.

As postnatal follow-up visits will not require treatment to be taken, any adverse events occurring during this time will not be recorded in the trial database.

If any abnormality is found in the bloods, blood pressure or echocardiograms at any point during active treatment or postnatal follow-up, this will be explained to the participant and we will inform their GP or refer to the appropriate clinical team depending on the clinical significance of the finding.

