### Adverse event reporting and harms {22}

Adverse events are collected for MIMICH study participants and their babies, from consent (from birth for babies) up to primary discharge after birth. AEs are commonly encountered in this population of pregnant women as a part of the clinical condition of pregnancy and diabetes in pregnancy. As the safety profile of metformin is well-characterised, a strategy of targeted reporting of AEs is used without affecting the safety of participants. Adverse events are separated into expected AEs, which are recorded on the case note review but not reported, and those that are reportable.

The following are considered expected in this population of pregnant women or a result of the usual clinical care and, as such, will be recorded in the participant’s medical record (including where a woman offers information to a research team) but not reported as (S)AEs:

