#### Maternal events

Intolerance to metformin (usual care arm)Episodes of hypoglycaemia (not requiring hospitalisation)Admission in active labourAdmission for cervical ripening or induction of labourAdmission for caesarean sectionAdmission for assessment for suspected foetal compromise, including poor growth, or reduced foetal movementsAdmission for the treatment of infection/sepsisAdmission for monitoring for diabetes, hypertension or pre-eclampsia, antepartum haemorrhage, suspected preterm labour, pre-labour rupture of the membranes or other reasons for monitoringAdmission for psychiatric or social reasonsAdmission for unstable lie or external cephalic versionAdmission for postpartum complicationsKnown complications of pregnancy that are collected for every woman as part of outcome collection (including, but not limited to, pre-eclampsia, postpartum haemorrhage, postpartum haemorrhage requiring transfusion or hysterectomy)Any adverse event that is expected during pregnancy including but not limited to tiredness, constipation and back pain. Maternal undesirable effects of the allocated medication regime will be recorded at each trial visit

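### The exemption of metformin intolerance from adverse-event reporting is tied to the usual care arm, although metformin use is expected in both arms

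*Protocol article*

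**What the plan says.** The exemption appears twice in the protocol article, each time with the arm attached. Section {11b} says: "Failure to tolerate metformin (usual care arm) will not be reported as an adverse event unless related to a reportable serious adverse event". The Maternal events list under Adverse event reporting and harms {22} includes "Intolerance to metformin (usual care arm") among the events that go into the medical record but are not reported as (S)AEs. The effect of being on that list is set out just before it: "Adverse events are separated into expected AEs, which are recorded on the case note review but not reported, and those that are reportable".

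Section {11b} also says that "it is anticipated that some participants will need to take metformin in the intervention arm".

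Under Outcomes {12}, the Adverse events paragraph sets the count: "Adverse event recorded (number of women and number of adverse events) during treatment only". It adds that "All AEs and SAEs identified will be recorded in the trial database". The section on the coordinating centre and steering committee {5d} has the oversight committee review rates of adverse outcomes, in reports split by arm with the allocation label removed.

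Two further provisions bear on the point. The Maternal events list ends: "Maternal undesirable effects of the allocated medication regime will be recorded at each trial visit". The prespecified secondary outcomes under Outcomes {12} include undesirable effects, defined as "number of women reporting undesirable effects associated with metformin and/or insulin/number of women receiving metformin or insulin treatment".

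**The concern.** An adverse-event rule should depend on the event or on the drug taken, so that the same event is classified in the same way in each randomised group. Here it depends on the arm. A usual-care woman with non-serious metformin intolerance is exempt. A withheld-arm woman who is given metformin and has the same reaction is not on the exempt list as worded.

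The trial is open-label, so staff classify events knowing the arm. If the bracket is applied literally, the number of women with an adverse event and the number of events are collected under different rules in the two groups. The distortion runs one way: it can add events to the withheld arm that would not be counted in usual care, and so makes withholding metformin look relatively worse. What is at stake is the comparability of the adverse-event table and of the oversight reports. The efficacy result is not at stake.

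**Working it through.** The protocol states no figure for this point, so there is nothing to reproduce. The check sets the provisions side by side and then gives an illustration under stated assumptions.

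**Step 1. Classification of the same event, non-serious metformin intolerance**

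| | Usual care | Withheld arm, metformin taken |
|---|---|---|
| Metformin exposure foreseen? | Yes, as allocated | Yes, section {11b} |
| Exempt under {11b} as worded? | Yes | Not named |
| On the expected maternal events list as worded? | Yes | Not named |
| Visit record of undesirable effects | Yes, metformin belongs to the allocated regime | Unclear, metformin is not the allocated regime |
| Secondary outcome on undesirable effects | Yes, as a woman receiving metformin | Yes by the definition, though its label refers to allocated treatment |

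The first three rows show the asymmetry. The last row shows that the definition of the secondary outcome already goes by drug received. The fourth row shows that the visit record is worded more narrowly than the outcome it feeds.

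**Step 2. Does the asymmetry reach the adverse-event count?** The Adverse events paragraph sends every identified AE and SAE to the trial database. Section {22} sends expected events to the case note review without reporting. The text does not say whether exempt events enter the count of women and events. If they do, the count itself is even-handed. If only reportable events are counted, the asymmetry carries through.

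**Step 3. Size, if only reportable events are counted**

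Inputs:
- Women per arm: 225 / 2 = 112.5 (target sample, 1:1 allocation).
- Share *c* of the withheld arm that takes metformin: not given; assumed 5% to 30%.
- Share *t* of metformin users who are intolerant: not given; assumed 5% to 30%.

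Withheld-arm women with a reported intolerance event = 112.5 × *c* × *t*:

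| *c* | *t* | Women |
|---|---|---|
| 5% | 5% | 0.3 |
| 10% | 10% | 1.1 |
| 20% | 20% | 4.5 |
| 30% | 30% | 10.1 |

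The usual-care count for the same event is 0 throughout. The false excess is therefore 0.3 to 10.1 women, or *c* × *t* = 0.25% to 9% of the arm.

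**Step 4. What the arm restriction does not cause.** If every usual-care woman took metformin, 112.5 × 5% = 5.6 to 112.5 × 30% = 33.8 of them would be intolerant and unreported. That is the effect of having an exemption at all. It would be the same under an arm-neutral exemption, so it does not measure the asymmetry. It is also an upper figure, because Intervention description {11a} starts metformin only when diet and lifestyle measures fall short.

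**The case against.** The best defence is that nothing of substance is lost. Undesirable effects of metformin and insulin are a prespecified secondary outcome with women receiving those drugs as the denominator, and effects are recorded at each visit. Doses are also recorded at each visit, and changes from allocated treatment are documented, so crossovers can be identified. This stands as far as tolerability data are concerned. It does not make the adverse-event count even-handed. The outcome's denominator is a group formed after randomisation, its numerator pools the two drugs, and the visit record is worded for the allocated regime.

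A second defence is that the bracket may only name the arm in which metformin is the allocated drug. In {11b} it comes just after a sentence on usual-care women who cannot tolerate metformin. Section {22} also introduces its list as covering events that result from usual clinical care, and {11b} calls switching of treatment a common part of such care. This too stands: no sentence says that intolerance in the withheld arm is to be reported. That reading is inferred from the bracket.

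Third, targeted reporting is a reasoned choice for a drug with a well-known safety profile in a trial classed as low risk, and intolerance related to a reportable SAE stays reportable. This is accepted. The point concerns the arm restriction, not the exemption.

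A reader might go further and infer that insulin reactions, lacking a matching exemption, count against the withheld arm. The documents do not support this. Insulin is used in both arms, the exempt list covers non-hospitalised hypoglycaemia in both, and it has an open-ended item for expected events. A reader might also conclude that adverse-event counts by arm are biased as a matter of fact. That needs a crossover rate and a counting rule that the article does not give.

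**Conclusion.** The point holds as a modest defect in a reporting rule. The exemption is worded for one arm in two places while the protocol foresees metformin use in both, so adverse-event counts and per-arm oversight reports can be distorted in favour of usual care. The effect is probably small: about 0.3 to 10 women in the withheld arm. This assumes 5% to 30% crossover to metformin, 5% to 30% intolerance among users, a literal reading of the bracket, and a count limited to reportable events. If exempt events do enter the count, or if staff already apply the exemption to both arms, the distortion disappears. The document settles neither question. The primary outcome and the capture of tolerability are not undermined. The change is worth making because it is cheap and removes an arm-dependent rule from an open-label trial.

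**What to change.** 1. In section {11b} and in the Maternal events list, make the exemption apply to non-serious metformin intolerance in either arm, by drug received. Keep the existing exception for events related to a reportable SAE.
2. In the Maternal events list, have the visit record cover undesirable effects of treatment received rather than only of the allocated regime, in line with the definition of the secondary outcome.
3. Tabulate those undesirable effects by randomised arm beside the adverse-event counts, so that a reader sees the exempt events in both groups.

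The cost is a small wording change in the reporting provisions and one extra table row. No new visit is needed, and no treatment rule changes. If recruitment has closed (the article expected this by March 2025), the tabulation can still be added, since doses and treatment changes are recorded and crossovers can be identified.

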### Strategies to improve adherence to interventions {11c}

As a pragmatic trial, standard clinical advice on adherence to diabetes treatment will be advised and encouraged at every visit with no additional specific trial advice given. The daily dose of metformin (0–2.5 g), long- and short-acting insulins taken over the preceding week will be recorded at each study visit.

